### Sample size calculation

The sample size calculation for this study was based on data obtained from a pre-trial conducted between October 2024 and January 2025. In the pre-trial, 24 post-stroke tracheostomy patients meeting the study’s inclusion and exclusion criteria were enrolled and randomly assigned to either the TFRL-IMT group (*n* = 12) or the conventional treatment group (*n* = 12). In the conventional treatment group, 6 patients were successfully extubated, resulting in a 50% decannulation success rate. In the TFRL-IMT group, 10 patients were extubated, with an decannulation success rate of 83.3%. The between-group difference in decannulation success rates was 33.3%. Based on the preliminary results and relevant literature (5), the decannulation success rate was conservatively estimated to be 50% in the control group and 80% in the TFRL-IMT group, yielding an expected effect size of 30%.

The sample size was calculated using PASS 15.0 software (NCSS, LLC, Kaysville, UT, United States). A significance level of *α* = 0.05 (two-sided) and statistical power (1 − *β*) = 80% were adopted based on literature recommendations (27). Assuming an decannulation success rate of 50% in the control group and 80% in the TFRL-IMT group, the required sample size for each group was calculated to be 26. Based on the preclinical follow-up experience of the research team, an expected attrition rate of 15% was applied. According to the adjustment formula *n*’ = *n*/(1 − f), where *n* is the unadjusted sample size and f is the expected attrition rate (28), the adjusted sample size per group was calculated as *n*’ = 26/(1–0.15) ≈ 30. Therefore, the finalised total sample size was determined to be 60.

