### Randomisation and blinding

This study will adopt a stratified block randomized controlled design, with participants randomly assigned to the experimental or control group in a 1:1 ratio. Two stratification factors, age (≤40 years vs. >40 years) and stroke type (ischemic vs. hemorrhagic), will be incorporated into the randomization process to ensure balanced distribution of key prognostic variables between groups. The random allocation sequence will be generated using a computer-based random number generator, and group assignment will be conducted by an individual independent of the study team to ensure allocation concealment.

Owing to the nature of the intervention, blinding of participants and treatment providers will not be feasible. To minimise measurement bias, a strict single-blind design will be employed: all outcome assessments will be conducted by independent, standardised assessors who will remain blinded to group allocation; data entry will be performed by research assistants blinded to group allocation; and statistical analyses will be conducted independently by statisticians not involved in the research team. In addition, all research team members, except those directly administering the intervention, will remain blinded to group allocation throughout the trial.

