#### Primary outcome

The primary outcome will be the decannulation success rate following the 3-week intervention. Successful decannulation will be defined as the absence of reintubation within 72 h following tracheostomy tube removal. The decannulation process will adhere to a strictly standardised protocol, with specific criteria as follows: minimal secretions with effective clearance; good cough function (peak cough flow >160 L/min); absence of hypoxaemia (SpO2 ≥ 92%), respiratory distress, or reduced level of consciousness during a 24 h continuous tracheostomy tube occlusion test; and normal swallowing function. The decannulation success rate will be calculated as the proportion of successful decannulation relative to the total number of cases treated and expressed as a percentage. This outcome will be assessed at the end of the 3-week intervention.

Decannulation failure will be defined as the occurrence of any of the following conditions within 72 h post-decannulation: severe respiratory distress (respiratory rate >35 breaths/min); persistent hypoxaemia (requiring FiO2 > 0.5 to maintain SpO2 ≥ 90%); hypercapnia (PaCO2 > 50 mmHg and pH < 7.30); or clinical need for reintubation.

To ensure objectivity and accuracy, decannulation decisions will be made jointly by at least two therapists and rehabilitation physicians who are blinded to patient group allocation. This double-blind assessment design minimizes bias and enhances the reliability of study outcomes.

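### By the protocol's own attrition formula 26 becomes 31 per group, not 30, so a total of 60 covers 13.3% attrition and not the stated 15%

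*Protocol article*

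**What the plan says.** Everything needed for the check is printed in the protocol article under Sample size calculation. The planning rates are given as follows: "Assuming an decannulation success rate of 50% in the control group and 80% in the TFRL-IMT group". The test is two-sided at 0.05 with 80% power, and "the required sample size for each group was calculated to be 26". Then "an expected attrition rate of 15% was applied", using n' = n/(1 − f). The result is shown as approximately 30 per group, and the section closes: "Therefore, the finalised total sample size was determined to be 60". Allocation is 1:1 (Randomisation and blinding).

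Two other places bear on how dropouts enter the analysis. Under Primary outcome, the success rate is "the proportion of successful decannulation relative to the total number of cases treated". Under Statistical analysis, the effect is assessed by both intention-to-treat and per-protocol. Missing data are handled mainly by mixed-effects models assuming missing at random, with multiple imputation and complete cases as sensitivity analyses.

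**The concern.** A formula, its two inputs and its result are printed together, and the result does not follow. Rounding 30.59 to the nearest whole patient gives 31, and so does rounding up, which is usual for a sample size. Only truncation gives 30. The protocol therefore claims protection against 15% attrition that its own total does not quite provide.

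The stake is the accuracy of a stated design figure. The total of 60 is repeated in the Abstract and under Participants and recruitment, and readers will take it as delivering 80% power after 15% loss.

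**Working it through.** **Inputs**, all from Sample size calculation: n = 26 per group, f = 0.15, rates 50% and 80%, two-sided alpha 0.05, power 80%.

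**1. The attrition step, taking 26 as given.**
- n' = 26/(1 − 0.15) = 26/0.85 = 30.59, so 31 per group and 62 in total.
- The printed 30 is reached only by truncating. Multiplying instead, 26 × 1.15 = 29.9, would also round to 30, but that is not the printed formula.

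**2. What 30 per group covers.**
- 30 × 0.85 = 25.5 per group, or 60 × 0.85 = 51 in total, against the plan's 26 and 52.
- Attrition covered: 1 − 26/30 = 4/30 = 13.3%, i.e. 4 per group.
- Check at 31: 31 × 0.85 = 26.35, which is above 26.

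**3. What the rounding is worth.** Power for 80% vs 50%, two-sided uncorrected chi-square test, by exact enumeration of both binomial distributions, with the normal approximation alongside:

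| Analysed per arm | Exact | Normal approximation |
|---|---|---|
| 26 | 65.4% | 62.7% |
| 30 | 69.2% | 69.2% |
| 31 | 71.4% | 70.7% |

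Going from 30 to 31 adds about 2 points by exact power (1.5 by the approximation).

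**4. The base of 26.** This matters because correcting only the rounding would leave it standing. The pooled chi-square formula is n = [1.960 × √(2 × 0.65 × 0.35) + 0.842 × √(0.50 × 0.50 + 0.80 × 0.20)]² / 0.30². The bracket is 1.322 + 0.539 = 1.861. Its square, 3.463, divided by 0.09 is 38.5, so 39 per group. Other standard versions give 36 (unpooled), 38 (arcsine) and 45 (continuity-corrected). None gives 26.

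**5. A worst case, by assumption only.** Suppose 15% of each arm is lost before the primary endpoint, every lost patient counts as not successful, and the planning rates do not already include such patients.
- 0.80 × 0.85 = 0.68 and 0.50 × 0.85 = 0.425, a difference of 25.5 points.
- Exact power at 30 per arm is then 52.1%.

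**The case against.** The strongest reply is that this is trivial. The shortfall is half a patient per group, the protocol uses an approximation sign, and the 15% is itself a judgement from the team's follow-up experience. All of that is fair, and it keeps the point minor. It does not make the printed result correct.

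Two stronger readings are tempting, and the documents support neither.

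- *That attrition cuts power to about 52%.* A reader might infer this because the primary rate is taken over all cases treated and the analysis is by intention-to-treat, while dividing by 1 − f presumes that dropouts leave the analysis. The two are indeed not aligned. But the article nowhere says that a dropout counts as a failure, and its missing-data approach points to missing at random, under which the rates are not diluted. In the complete-case sensitivity analysis, dividing by 1 − f is the right allowance. The pilot rates behind the planning values, 6/12 and 10/12, already use every randomised patient, so shrinking them by 15% may count attrition twice. The 15% may also fall after the primary endpoint, which comes at the end of three weeks of supervised treatment plus 72 hours, whereas follow-up runs to three months. If all 30 per arm had known outcomes at the planning rates, 30 would exceed 26.
- *That 31 per group is the right sample size.* It is only what the printed formula returns from 26. It does not reach 80% power, for the reason in step 4 of the working.

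**Conclusion.** The figure is wrong as written, and the error is minor. By the protocol's own formula the result is 31 per group (62 in total), and 60 patients cover 13.3% attrition. This needs no assumption beyond the printed inputs. The rounding itself is worth about 2 points of power.

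The power that 60 delivers for 80% vs 50% is about 69% if all 30 per arm are analysed and about 65% if 26 completers per arm are. Both assume the planning rates and the uncorrected chi-square test. The 68% vs 42.5% scenario with about 52% power is a worst case that depends on all three assumptions in step 5 and on equal loss in the two arms. It should not be read as the trial's expected power.

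**What to change.** In Sample size calculation, do one of two things:

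- keep 60 and state that it covers 13.3% attrition (4 per group); or
- print 31 per group (62 in total) as the result of the formula.

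In either case, add the power that 60 delivers in the denominator actually used for the primary analysis, and do not imply that 26 or 31 per group reaches 80%. For example: about 69% with all 30 per arm analysed and about 65% with 26 completers per arm. If the 52% scenario is reported, label it a worst case and list its assumptions. The correction belongs with any revision of the base figure of 26, so that the same rounding is not carried over.

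The cost is a wording change. No extra patients are needed if the figures are restated; the downside is that the stated figures become slightly less favourable.

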### Randomisation and blinding

This study will adopt a stratified block randomized controlled design, with participants randomly assigned to the experimental or control group in a 1:1 ratio. Two stratification factors, age (≤40 years vs. >40 years) and stroke type (ischemic vs. hemorrhagic), will be incorporated into the randomization process to ensure balanced distribution of key prognostic variables between groups. The random allocation sequence will be generated using a computer-based random number generator, and group assignment will be conducted by an individual independent of the study team to ensure allocation concealment.

Owing to the nature of the intervention, blinding of participants and treatment providers will not be feasible. To minimise measurement bias, a strict single-blind design will be employed: all outcome assessments will be conducted by independent, standardised assessors who will remain blinded to group allocation; data entry will be performed by research assistants blinded to group allocation; and statistical analyses will be conducted independently by statisticians not involved in the research team. In addition, all research team members, except those directly administering the intervention, will remain blinded to group allocation throughout the trial.

### Intervention protocol

#### Experimental group interventions

In this study, patients in the experimental group will receive TFRL-IMT in addition to conventional treatment. TFRL-IMT will be administered using the inspiratory muscle training module of a portable pulmonary function testing device (X1, Seck Medical Devices Co., Ltd., Xiamen, China). The initial training load will be set at 30% of the subject’s MIP, which will be measured using the device’s built-in function. During the study period, MIP will be measured weekly, and the training load will be adjusted to 30% of the current MIP. Additionally, resistance will be gradually increased by 5% per week until 60% of MIP is reached and maintained, depending on the patient’s tolerance.

The training programme will last for 3 weeks, during which patients will undergo two sessions per day, each comprising five sets of six maximal inspiratory efforts with a one-minute rest between sets. During each session, the patient’s tracheal cannula will be connected to the device valve via a specialized connecting tube, and the patient will be instructed to inhale as forcefully and rapidly as possible, followed by slow exhalation. All training will be conducted under the supervision of healthcare professionals to ensure training quality and patient safety. The rehabilitation therapist will document the actual load, completion status, and any adverse events during each training session.

In patients with concurrent respiratory infections, appropriate antibiotics will be administered based on clinical manifestations and sputum culture results. In patients with thick sputum, nebulized salbutamol (2.5 mg) combined with ipratropium bromide (0.5 mg) will be administered three times daily at 8:00 a.m., 12:00 p.m., and 8:00 p.m.

To evaluate the efficacy and safety of the intervention, MIP values will be measured before and after training using the same portable pulmonary function device. Simultaneously, vital signs such as including heart rate, blood pressure, respiratory rate, and oxygen saturation will be continuously monitored.

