**Methods and analysis:**

This investigation will employ a single-center, assessor-blinded, parallel-group randomized controlled trial design, enrolling 60 post-stroke tracheostomy patients (planned age range 18–70 years; and gender distribution will be collected and analyzed). Stratified compartmental group randomization will be utilized to allocate participants to either the experimental (*n* = 30) or control group (*n* = 30) in a 1:1 ratio. Both groups will receive conventional treatment, while the experimental group will additionally undergo TFRL-IMT using an electronic device that provides inspiratory resistance which dynamically decreases with increasing lung volume for a duration of three weeks. The primary outcome measure will be the rate of successful decannulation, with secondary outcomes encompassing diaphragm function, respiratory parameters, clinical outcomes, and quality of life assessments. The primary outcome (decannulation success rate) will be compared between groups using the Chi-square test.

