This study considers the potential mechanisms by which TFRL-IMT improves clinical outcomes as follows. The electronically controlled resistance valve system delivers a flow resistance load that varies with lung volume and conforms to the pressure–volume relationship of the respiratory muscles (24, 25), thereby optimizing the training load, which ensures that the respiratory muscles receive appropriate stimulation at different levels of lung volume, and inducing comprehensive neuromuscular adaptations (23, 29). Compared with traditional methods, TFRL-IMT enables greater lung volume expansion and higher inspiratory flow rates at the same training intensity (23), thereby enhancing tolerance to higher training loads and increasing the total workload (25). This physiological advantage facilitates the enlargement of respiratory muscle fiber cross-sectional area (30) and improvement in oxidative capacity (31), thereby strengthening overall respiratory muscle function. Moreover, load parameters scientifically set according to respiratory physiology principles (30% of MIP) induce adaptive changes in respiratory muscles while minimizing the risk of overfatigue (32). From a neurophysiological perspective, regular inspiratory muscle training can reshape the central nervous system’s control mode of the respiratory muscles (33, 34), enhance motor unit recruitment efficiency (35, 36), and contribute to the reconstruction of respiratory neural circuits after stroke (37). Furthermore, enhanced diaphragm function improves alveolar ventilation and enhances coughing ability and reduces the risk of infection (38), while the optimisation of oxygenation status brought about by improved respiratory function can reduce the inflammatory response, which in turn indirectly promotes neurological function recovery (39).

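### From week 2 the training load has no single definition (30%, about 33% or 40% of MIP by week 3), and the stated 60% cannot be reached in a 3-week programme

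*Protocol article*

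**What the plan says.** All the operative text is in the protocol article, under Experimental group interventions.

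- Start: "The initial training load will be set at 30" per cent of MIP, measured with the device itself.
- Weekly adjustment: MIP is re-measured each week, and "the training load will be adjusted to 30% of the current MIP".
- Weekly progression, in the very next sentence: "resistance will be gradually increased by 5% per week until 60% of MIP is reached and maintained, depending on the patient"'s tolerance.
- Length: "The training programme will last for 3 weeks". The abstract agrees: "for a duration of three weeks".

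The Discussion returns to the load twice. The paragraph on mechanisms refers to "load parameters scientifically set according to respiratory physiology principles (30% of MIP"), with no progression and no 60%. The paragraph on design strengths says that the load follows the patient's own MIP percentage but gives no figure.

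The experimental group section also requires the therapist to record the load actually used at each session.

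**The concern.** The load is the main dose variable of the only component that separates the two arms. From week 2 the article gives two instructions for it, and neither is said to take precedence. A load set to 30% of the current MIP is not also 35% or 40% of it. The progression rule can itself be read in two ways, because 5% has no unit. Its end point, a 60% load that is attained and then held, does not fit the stated duration.

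This is not detail left to a fuller document. The article states the rule, and the statements conflict with each other and with the length of the programme.

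At stake are three things: whether therapists working from the same text deliver the same load, whether adherence to the load can be judged, and whether others can repeat a programme that the Introduction and Discussion both present as standardised.

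**Working it through.** **Inputs, all from the protocol article.** Starting load 30% of MIP; weekly reset to 30% of current MIP; weekly increase of 5%, unit not given; end load 60% of MIP; duration 3 weeks.

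**Load in week w as % of current MIP.** The first step is taken at the start of week 2, so w − 1 steps have been taken.

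| Reading | Formula | Week 1 | Week 2 | Week 3 |
|---|---|---|---|---|
| Weekly reset | 30 | 30 | 30 | 30 |
| Relative 5% | 30 × 1.05^(w−1) | 30 | 31.5 | 33.1 |
| 5 percentage points | 30 + 5(w−1) | 30 | 35 | 40 |

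The readings agree in week 1 only. In week 3 the ratio of highest to lowest is 40/30 = 1.33.

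**Can the plan's own 60% be reproduced?** No.

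- Percentage points: (60 − 30)/5 = 6 steps, so 60% is first reached in week 7.
- Relative: ln(60/30)/ln(1.05) = 0.693/0.0488 = 14.2, so 15 steps.
- Allowing a third step at the very end of week 3: 30 + 3 × 5 = 45%, or 30 × 1.05³ = 34.7%. Both remain below 60%.
- If the absolute resistance rises 5% a week and is not re-scaled to MIP, the load equals 60% of current MIP only if MIP falls to 30 × 1.05²/60 = 0.55 of baseline (two steps) or 30 × 1.05³/60 = 0.58 (three steps).

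**Size in pressure units (illustration only).** The article gives no MIP values. Assume a baseline MIP of 40 cmH2O and two cases for its course.

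| Assumed MIP course | MIP in week 3 | Reset, 30% | Relative, 33.1% | Points, 40% | 60% |
|---|---|---|---|---|---|
| Unchanged | 40 | 12.0 | 13.2 | 16.0 | 24.0 |
| Rising 10% per week | 40 × 1.1² = 48.4 | 14.5 | 16.0 | 19.4 | 29.0 |

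The ratios between readings do not depend on the assumed MIP.

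**The case against.** The best defence is that the two sentences are meant to be read together. The second opens with *Additionally* and ends with a tolerance clause. One could therefore re-anchor the load to the newly measured MIP each week, then add the step, and treat 60% as an upper limit. As the load is expressed as a percentage of MIP, percentage points would be a natural unit, giving 30, 35 and 40%. A limit that is never reached changes no load delivered. The mechanisms paragraph in the Discussion is a rationale rather than a dosing instruction, and it does not say that 30% is held throughout.

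Much of this is fair. It shows that a partly coherent reading exists, and that the Discussion is supporting evidence rather than a third rule. It does not settle the matter. The first sentence sets the load to 30% of current MIP; it does not say that the current percentage is re-scaled. Wording in which 60% is reached and then maintained presupposes that it is attained. The tolerance clause can explain slower progression but not faster. If the combined reading is intended, the text has to say so.

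Four stronger conclusions might be inferred, and the document does not support them:

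- *The tested intervention is undefined.* Device, starting load, weekly MIP measurement, session frequency, sets, repetitions, rests, supervision and duration are all stated. Only the load from week 2 is open.
- *The primary comparison is invalid.* Under Statistical analysis, intention-to-treat is one of the stated principles. It compares patients as randomised, whatever load was delivered.
- *The per-protocol set cannot be formed.* The article does not say that membership depends on load, and the definition may lie in a document not shown.
- *A claim about which load works is undermined.* The hypothesis compares the programme with conventional rehabilitation, and no dose-response analysis is planned.

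**Conclusion.** The point holds for the load from week 2 onward. The two consecutive sentences cannot both be followed literally, the unit of the increase is missing, and the 60% end load conflicts with the 3-week duration on every reading examined. The consequence is a planned week-3 load of 30%, about 33% or 40% of MIP.

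The timing assumption is that steps are taken weekly from the start of week 2. Allowing one more step raises the maxima to 34.7% and 45% and does not alter the conclusion. The pressure figures rest on assumed MIP values; the percentages do not.

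The harm is to uniform delivery, to judging adherence to the load, and to reproducing the programme. Session records let the delivered load be described afterwards, but they do not establish what was planned. The intention-to-treat contrast stands as a comparison of the programme as delivered.

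**What to change.** The clinical team should reconcile five elements into one weekly load rule: the weekly adjustment sentence, the progression sentence, the 60% figure, the 3-week duration, and the description of the load in the Discussion. The rule should give the 5% a unit and say how the weekly MIP measurement enters. Adherence to the load should then be assessed against that rule. Which of the conflicting elements gives way is a clinical decision, and no view is taken on it here.

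The cost is a wording amendment and a note to the treating therapists. The study period runs from March 2025 and the article appeared in September 2025, so patients may already have been treated. Their recorded session loads should be reported as delivered, together with the reading of the text in use at the time. No change to sample size, randomisation or the primary analysis follows from this point.
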